## Abstract

Previous research has demonstrated that exposure to outgroup descriptions that use person-first, as compared to identity-first, language can attenuate negative stereotypes or prejudice and enhance support for policies that seek to advance outgroup rights. However, those benefits of person-first language may not apply to all social groups equally. The present study examines a boundary condition of the effects of person-first language. Specifically, we postulate that person-first language reduces the stigmatization of outgroups to a lesser degree if individuals hold more important negative attitudes towards the respective communities. We will test this hypothesis in a two-factorial 2 (target group) x 2 (descriptor) online experiment that includes a control group and for which we will recruit a general-population sample (*N* = 681). Stereotyping, dehumanization, as well as negative affect and behavioral intentions towards two outgroups will be compared: people with a physical disability/the physically disabled (i.e., negative attitudes are expected to be less important) and people who have committed a violent crime/violent criminals (i.e., negative attitudes are expected to be more important). Our findings will bear implications for understanding when language use could influence public opinion of different social groups. Additionally, the research can inform the development of more effective communication policies to promote inclusion and reduce stigma.

## Introduction

In recent years, there has been a surge in guidelines that encourage the adoption of inclusive, non-stigmatizing language (e.g., [1–4]. Especially noteworthy is the recommendation to use person-first (or person-centered) instead of identity-first language; doing so has been most commonly suggested in medical and criminal justice contexts [5]. In practice, when communicating with or about an individual, it is, for example, recommended to say "person with autism" and not "autistic". Or, rather than "ex-convict", the phrase "person who was formerly incarcerated" is preferred (i.e., a post-modified noun that refers to a person is followed by a descriptor).

Despite criticism of person-first language policies [6–8], empirical evidence points to its benefits. More precisely, exposure to outgroup descriptions that employ person-first language has been found to reduce negative outgroup stereotypes, prejudice, and stigma (e.g., [9–12]. Having said this, it is also evident that person-first language may not affect perceptions of and attitudes or behavior towards all social groups equally. St. Louis [13] showed that across 12 different descriptor pairings, person-first language evoked more positive impressions for only two outgroups—“persons with leprosy” and “persons with psychosis”. Additionally, effect sizes that were attained in studies that explored the influence of person-first language in medical and criminal justice contexts varied widely [11, 14]. The reasons for those differential result patterns were not examined systematically.

The present research addresses this gap in the literature. Specifically, we investigate whether attitude importance moderates the effects of person-first language such that the latter are weaker for outgroups towards which individuals hold more important negative attitudes [15, 16]. Testing this hypothesis, we will recruit a general-population sample and conduct an online experiment to compare negative and positive stereotyping, dehumanization, negative affect, and behavioral intentions directed at others who have committed a violent crime/violent criminals (i.e., negative attitudes are expected to be more important) and people with a physical disability/the physically disabled (i.e., negative attitudes are expected to be less important).

## Person-first language and its benefits

Efforts to promote person-first language [1–4], which have their origins in the disability rights movement in the 1970s, the 1980s Denver Principles, as well as prison reform and Black liberation movements in the 1960s-70s [17], aim to alleviate stigmatization and its detrimental implications on mental/physical health, access to support, and social inclusion [17, 18]. Referring, for instance, to someone as “a person with an addiction” is thought to emphasize their personhood over the illness; their “humanity (and dignity is preserved) while promoting … individuality” [7, p. 258]. Moreover, person-first language is expected to ensure that addictive behavior, in this example, is viewed as just one of many actions that shape the person’s identity [5, 19]. In avoiding essentialization, it is indicated that the stigmatized characteristic or behavior can be changed [6].

To date, empirical evidence that confirms the benefits of person-first language is limited to studies that have examined its influence on outgroup perceptions, attitudes, and behavioral intentions [20–23] (see Lynch and Groombridge [24] for nil effects and Feldman et al. [25] who demonstrated no relationship between the *use* of person-first language and attitudes towards individuals with disabilities). Ashford and colleagues [9] employed the Go/No-Go Association Task to compare implicit negative biases towards individuals described by the terms "substance abuser" or "person with substance use disorder". The authors found significantly more negative implicit outgroup attitudes associated with the label "substance abuser". Endorsing these findings, “addicts” were viewed as more inferior than “people with addiction”, and participants endorsed maintaining social distance to “addicts” more strongly; sympathy and helping intentions were also lower for “addicts” [10]. Furthermore, a study that recruited professional counselors reported that participants expressed higher levels of tolerance towards “people with mental illnesses” than “the mentally ill” [14].

Beyond the medical domain, the effects of person-first language have been documented in two studies pertaining to the criminal justice context as well [18, 26]. Reading instructions that referred to another individual as an "offender" elicited more stigma and negative judgments than instructions that made reference to a "person with a conviction" [11]. Describing individuals either as a “returning citizen”, “a person who was formerly incarcerated” (i.e., two different person-first descriptors), or an “ex-convict” (i.e., identity-first descriptor) also affected outgroup perceptions and intentions to support reintegration efforts [12]. Notably, negative stereotypes were increased, willingness for social closeness reduced, and reintegration measures were less endorsed when participants were exposed to an identity-first descriptor [12].

## Criticism of person-first language

Despite those promising findings, person-first language has also attracted criticism. First, identity-first, not person-first, language is thought to enable a higher expression of agency and autonomy, allowing individuals and communities with lived experience to claim terms like “autistic” or “disabled” [20]. Moreover, it has been argued that separating a person from, for instance, their smoking behavior could suggest that the individual is otherwise not valuable [6]. Additionally, person-first language might, in fact, highlight that certain behaviors or qualities are negative, thus promote stigmatization [20, 21]. Speaking to this point, Gernsbacher [8] showed that person-first language was “more frequently (used) to refer to children with disabilities than to refer to children without disabilities” (para. 8), and was, overall, more frequently used to denote more stigmatized characteristics.

Relatedly, person-first language might not always align with someone’s self-image [6] or how people prefer to describe themselves. A study with participants who had received an autism diagnosis [27] demonstrated that there were no differences in the preference of the terms “autistic”, “person on the autism spectrum”, or “autistic person”; however, the aforementioned three terms were more preferred than “person with autism”, “person with autism spectrum disorder”, and “person with autism spectrum condition”. Thus, person-first language was evaluated less positively than identify-first language if it specified a disorder or condition [27, 28].

## Generalizing the person-first language effect

A further concern regarding the use of person-first language that has not been explored systematically pertains to the generalizability of its benefits. In reviewing the literature, it is evident that person-first language does not affect outgroup attitudes and behavioral intentions to the same degree across different social groups. For example, the prevalence of negative implicit associations differed to a moderate extent between participants exposed to the terms "substance abuser" or "person with a substance use disorder" (d = .39; [9]). A moderate-large difference in levels of sympathy or willingness to help was documented when others were described as "addicts" instead of "people with addiction” (d = .61; [10]; see Granello and Gibbs [14] for moderate-large effects when comparing attitudes towards “people with mental illnesses” and “the mentally ill”). Exposure to person-first rather than crime-first language, in turn, led to only a small decrease in perceived recidivism risk of violent offenders (d = .21; [11]). The same study showed that person-first language did not at all impact perceptions of those who had committed nonviolent property or drug offenses ([11]; see Jackl [12] for further small effects comparing person- or crime-first language).

Similarly, St. Louis [13] demonstrated that person-first language evoked more positive outgroup impressions for only two of twelve descriptor pairing–“person with leprosy”/”leper” and “person with psychosis”/”psychotic”. These findings were attained in a diverse sample that included individuals with a language-disorder, parents of clients, speech-language pathology students, and the general public. St. Louis [13] did not elaborate on why person-first language effects were not identified for all descriptor pairings.

## Attitude importance as a moderator of the effects of person-first language

Advancing the literature, we seek to investigate one potential explanation for the differential result patterns presented in the previous section. As noted, person-first language is expected to attenuate stigmatizing views (and behavior) such that different, more humanizing outgroup attitudes (and actions) are adopted. However, exposure to outgroup descriptions that use person-first language should only influence attitudes, or influence those attitudes more substantially, that are, in fact, malleable. A burgeoning body of research confirms that the latter is not the case for all viewpoints. Specifically, there is evidence to suggest that attitudes that are *stronger* are more resistant to change [29–33].

Attitude strength is distinguished from valence. Even if two persons evaluate an object negatively (i.e., same valence), the strength of the respective negative attitudes can vary [34]. Attitude strength also varies between objects, and someone might hold stronger and weaker attitudes about different objects [16]. Furthermore, groups of people (i.e., issue publics; [35]) may be characterized by equally strong attitudes towards the same object [36], attitude strength fluctuates collectively in line with the political climate and public attention on certain issues.

A common operationalization of attitude strength is attitude importance, that is, “the subjective sense of concern, caring, and the significance that an individual attaches to an attitude (towards a given object)” ([37], p. 209). Boninger and colleagues [38] stipulated that attitude importance reflects a belief about the significance of an attitude for oneself and forms part of one’s self-concept [39]. This subjective judgment is thought to be independent of notions of descriptive or prescriptive importance (i.e., what attitudes most people attribute significance to or what is the right attitude to attribute significance to).

Three predictors of attitude importance have been identified [15]. An attitude is typically more important if the object it pertains to is of higher material self-interest (i.e., impacts the individual’s rights, privileges, or lifestyle), if the attitude (object) is of higher importance to a social group that the individual strongly identifies with, and if the attitude (object) reflects or makes reference to core moral, ideological, or aesthetic values [38]. Self-interest must be differentiated from being personally affected by a situation or condition (i.e., personal relevance/involvement) [15]. In Boninger and colleagues’ [38] seminal work it was also demonstrated that self-interest, social identification, and values influenced the importance of distinct attitudes to different degrees. On the issue of racial segregation, for example, self-interest primarily informed attitude importance; regarding the topic of abortion, self-interest and values predicted importance at comparable levels [38].

As noted earlier, a burgeoning body of research has shown that more important attitudes are more resistant to change even if the person is confronted with substantial contesting evidence [40]. In a field study that examined the impact of participating in a class on women’s studies on egalitarian attitudes, the latter were less affected if students viewed the class as more important [41]. In turn, inoculation (or forewarning) messages did not foster further resistance (i.e., predicted less attitude change) for individuals who considered their attitudes on the topic more important; forewarning did boost resistance for those who attributed low significance to the issue [42].

The persistence of more important attitudes has been primarily explained by focusing on cognitive processes. The elaboration likelihood model of attitude strength (Petty et al., 2009), for example, posits that information associated with important attitudes is processed in a more elaborate manner, which would enhance attitude accessibility and certainty, as well as knowledge about the attitude object. Indeed, important attitudes are typically more salient [32, 43]. However, affect appears to play a crucial role as well in maintaining more important attitudes. If an important attitude was contested, for instance, by counter-attitudinal information, more negative affective responses such as anger and irritation were evoked (counter-arguing/negative thoughts were also enhanced and the source was viewed less favorable); the affective responses partially explained the stability of more important attitudes [37, 39]. These findings align with cognitive dissonance theory [44] that postulates discomfort (i.e., an affect) after encountering attitude-inconsistent information, or behaving in an attitude-inconsistent manner, especially with respect to more important attitudes.

## The present research

The present research advances the literature by integrating evidence on the impact of person-first language with insights pertaining to the predictors and consequences of attitude importance. First, aiming to replicate previous studies, we postulate that one-time exposure to outgroup descriptions that use person-first language reduces negative outgroup stereotyping (*Hypothesis 1a*) and negative outgroup affect (*Hypothesis 1b*), and increases outgroup approach behavior intentions (*Hypothesis 1c*). We also consider further outcomes, which reflect several unexplored potential benefits of person-first language [5, 19]. More precisely, we assess if one-time exposure to outgroup descriptions that employ person-first language fosters stronger positive stereotyping (*Hypothesis 1d)* as well as lower levels of dehumanization of the target outgroup (*Hypothesis 1e*).

Second, we test a boundary condition of the influence of person-first language to investigate why its effects on outgroup perceptions or behavioral intentions vary in size across different social groups—especially when comparing research that was conducted in the medical and criminal justice context. As discussed, it is conceivable that individuals attribute different levels of importance to their attitudes towards various outgroups. An attitude towards an outgroup is expected to be more important if the outgroup’s actions impact the individual’s rights or lifestyle more strongly (i.e., self-interest); if the attitude about the outgroup is more important for a relevant reference group (i.e., social identification); and if the outgroup’s activities infringe strongly on the individual’s core values (i.e., values) [38].

Using concrete examples, even if both attitudes are negative in valance, attitudes towards an outgroup that is affected by disabilities are expected to be less important than attitudes towards others who have committed a crime. A person’s disability typically does not inflict restrictions on the lifestyle of the general public. Committing a crime, on the contrary, directly and indirectly affects third parties and can have severe negative implications for the quality of life in a neighborhood. The public in the United Kingdom (UK), where the present research will be conducted, also indicated in two recent polls that ‘crime’ was one of the five most important issue facing the country [45]; the economy, health, immigration, and the environment were viewed as more important; see also Office for National Statistics (ONS, [46]). Lastly, committing a crime violates universal moral values, core values of different religious communities, as well as the law in the UK. If attitudes towards individuals who have committed a crime are attributed a higher significance than attitudes related to other people with a disability, the former should be less likely to change even if one is exposed to an intervention that aims to reduce stigmatization. Therefore, the aforementioned effects of outgroup descriptions that use person-first language (*Hypothesis 1a -1e)* are expected to be smaller for the outgroup “people who have committed a violent crime” than “people who have a physical disability” (*Hypothesis 2*).

## Method

By virtue of this being a stage-1 registered report, the data for this study is not yet available. All data, analytical scripts, and materials will be made available on this Open Science Framework registry https://osf.io/u54k8/?view_only=66cd4d8abfd94c588603abece4a2afd9 upon study completion. The departmental ethics committee of the Department of Security and Crime Science, UCL has granted written ethical approval for this study.

### Design plan

To assess the hypotheses, we will conduct a single-blind (online) experiment; participants will not know to which condition they were assigned but researchers will be aware of the respective treatments when analyzing the data. We will apply a between-subjects design that includes two factors (i.e., target group x descriptor) with two levels respectively (target group: people who have a physical disability, people who have committed a violent crime; descriptor: identity-first, person-first) as well as a control group. Simple randomization will be implemented to assign participants.

### Sampling plan

As of the date of submission of this registered protocol, the data have not yet been collected, created, or realized.

#### Data collection procedure

Participants will provide informed consent through a tick-box. Data will be collected on the online opt-in access panel Prolific Academic. Participants will self-identify by responding to an invitation on the platform and will receive reimbursement of 0.50 GBP, corresponding with the anticipated study duration of five minutes. A pre-test, which will capture attitude importance, will be conducted one week before the main study.

#### Sample size

We aim to recruit *N* = 681 participants. The sample size calculation is based on an a-priori power analysis, considering the smallest effect of interest as a reference [47]. Our goal is to obtain .95 power, with α = .01 (Bonferroni-corrected p-value for five outcomes; see below), to be able to detect also small effects (or differences) of f = .175 with univariate analyses of variance (one-way). We will only recruit participants who are UK residents and older than 18 years. We introduce the former selection criterion (i.e., being a UK resident) as we will apply definitions of disability and violent crime (see Manipulated variables–experimental stimuli) that are provided by UK institutions.

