An attention check will be embedded in the list of aforementioned items (‘This is an attention check. Please answer ’Not at all’ to indicate that you pay attention.’). Lastly, participants will be asked to complete a manipulation check (‘You have just answered several questions about a specific group of people. How was this group referred to?’ Answer options: Violent criminals, People with a physical disability, Most people, The physically disabled, People who have committed a violent crime, My friends) and indicate whether they themselves have ever committed a violent crime (No/Yes) or describe themselves as a person with a physical disability (No/Yes).

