### Analysis plan

#### Data exclusion

We will exclude data from all participants who did not fully complete the study, failed either the attention or the manipulation check, or who indicated that they themselves had ever committed a violent crime or describe themselves as a person with a physical disability.

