#### Missing data

All questions will require responses, such that no missing data will occur. Incomplete responses will be removed (i.e., listwise deletion).

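### The recruitment target of 681 equals the number the power calculation needs in the analysis, so the stated .95 power does not hold once the planned exclusions are made

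*Protocol article*

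**What the plan says.** The Sample size section ties the recruitment target to the power analysis: "We aim to recruit *N* = 681 participants. The sample size calculation is based on an a-priori power analysis". The abstract uses the same figure in the same sense: "for which we will recruit a general-population sample (*N* = 681". The inputs are given as "Our goal is to obtain .95 power, with α = .01 (Bonferroni-corrected p-value for five outcomes; see below", to detect "small effects (or differences) of f = .175 with univariate analyses of variance (one-way". The only filters named at recruitment are UK residence and age.

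The exclusions come later. The Data exclusion section states: "We will exclude data from all participants who did not fully complete the study, failed either the attention or the manipulation check". It adds two grounds based on the participant's own status. According to the Measured variables section, these come from questions at the end of the main study, where people "indicate whether they themselves have ever committed a violent crime (No/Yes) or describe themselves as a person with a physical disability (No/Yes".

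No section gives an expected exclusion rate, increases the target to allow for exclusions, or says that excluded people will be replaced.

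**The concern.** A power calculation gives the number of people who must be in the analysis. The article uses that number as the count to recruit, then removes people on five grounds that can only be known after they have entered the study. Some loss is foreseeable. A general-population sample will include people with a physical disability, who are excluded by rule. The manipulation check asks participants to tell apart closely similar labels, so some may fail it.

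What is at stake is the accuracy of the stated .95. The article offers this power as its answer to the cost of the Bonferroni correction, so a reader of null results will rely on it.

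**Working it through.** **Inputs**
- From Sample size: f = .175, alpha = .01, target power .95, one-way ANOVA, 681 recruited.
- From Confirmatory analyses: three groups per ANOVA (identity-first, person-first, control), run once for each descriptor pairing.
- From Design plan: five arms with simple randomisation.
- Not in the article: the exclusion rate d. The values 5%, 10%, 20% and 30% are assumptions.

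**Formula.** Power of the omnibus F-test is P(F′ > F crit). F crit is the 1 − alpha quantile of the central F with k − 1 and N − k degrees of freedom. F′ is noncentral F with the same degrees of freedom and noncentrality λ = f² × N. Here f² = .175² = .030625.

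**Step 1: reproduce 681.** The smallest N that gives .95 power depends on the number of groups k:

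| k | minimum N |
|---|---|
| 2 | 586 |
| 3 | 679 |
| 4 | 747 |
| 5 | 802 |

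Only k = 3 leads to the article's figure: 679 rounded up to equal groups is 3 × 227 = 681. At N = 681, λ = .030625 × 681 = 20.86 and power is .9507. The margin is 681 − 679 = 2 people, or 2/681 = 0.3%. No allowance for exclusions is contained in the figure.

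**Step 2: apply exclusions on the same basis.** This keeps the plan's three-group calculation and changes only N, to 681 × (1 − d):

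| assumed d | N left | λ | power |
|---|---|---|---|
| 0% | 681 | 20.86 | .951 |
| 5% | 647 | 19.81 | .938 |
| 10% | 613 | 18.77 | .922 |
| 20% | 545 | 16.69 | .880 |
| 30% | 477 | 14.61 | .821 |

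**Step 3: recruitment needed for 681 analysed.** 681/(1 − d) gives 717, 757, 852 and 973 at 5%, 10%, 20% and 30%.

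**Step 4: what 681 analysed participants would deliver.** Each planned ANOVA uses three of the five arms. With equal expected arm sizes that is 681 × 3/5 = 408.6, about 409 people, and power is about .74 before anyone is excluded. Full power in each ANOVA would need five arms of 227, or 1135 analysed. This is a separate problem from exclusions, but it limits what correcting the recruited count can achieve.

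**The case against.** The strongest reply is that the verb recruit does not settle the matter. The sponsor may intend to replace excluded panel members, and a condensed article may leave that to a fuller document. This is fair against any claim that the analysed sample must fall short on every possible reading. It does not remove the point. The article gives the target, its derivation and the exclusion rules, and a study that follows them as written will not have the stated power once more than two people are excluded.

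A second reply is that the loss from exclusions alone is moderate. That stands: power stays above .9 at 10% and above .8 at 30%.

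Several stronger readings are tempting, but the article does not support them:
- A reader might attribute the whole fall from .95 to .74, and on to about .53 at 30% excluded, to the exclusions. The drop from .95 to .74 comes from the five-arm split and occurs with no exclusions at all.
- A reader might count drop-out in the week between pre-test and main study as a further loss. The Data collection procedure section does not say that 681 is counted at the pre-test, and the ANOVAs use main-study outcomes only.
- A reader might call "All questions will require responses, such that no missing data will occur" false. Forced responses do prevent item-level gaps among completers, and the same section goes on to say openly that incomplete records are removed. Counting break-offs by arm would be a reporting preference.
- A reader might propose screening on the two status questions at the pre-test. There the two target topics are mixed with three fillers, and direct questions about the participant's own violent crime and disability could reveal the targets before outcomes are measured.

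**Conclusion.** The point holds as a wrong power statement of moderate size. The recruited number equals the analysed number required, the exclusions follow recruitment, and no allowance or replacement is stated. On the plan's own three-group basis, the .95 becomes about .94, .92, .88 or .82 at 5%, 10%, 20% or 30% excluded.

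This rests on three assumptions: the exclusion rates, which the article does not give; exclusions spread evenly over the arms; and the omnibus F-test at f = .175 as the powered test. The conclusion would fall away if 681 were meant as valid completes with replacement, but the article does not say so. Even then, the .95 would not apply to any planned ANOVA, because of the arm split.

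**What to change.** Reword the Sample size section in one of two ways.

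1. **Restate the power.** Say that 681 is the number before exclusions, give the expected exclusion rate with its basis, and state the power for the number that will enter each three-arm ANOVA. As an illustration, at an assumed 10% excluded about 368 people enter each ANOVA (613 × 3/5) and power is about .68. Most of the difference from .95 is due to the arm split. This costs a few sentences and a less favourable power figure, and needs no extra participants.

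2. **Redefine the target.** Say that 681 means valid completes after the exclusions in the Data exclusion section, and that recruitment continues until that number is reached. At the assumed rates this means 36 to 292 extra recruits (717 − 681 to 973 − 681). At the stated 0.50 GBP each, if all are paid, that is 18 to 146 GBP before any platform charges. The text should add that this alone leaves about 409 per ANOVA and power of about .74, so the .95 still cannot be claimed.

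The status questions can stay where they are. The article states that no data have yet been collected, so either change can be made before recruitment starts.
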